### Secondary outcome measures

Secondary evaluation criteria are defined as follows:a)Performance of saliva sampling compared to NPA for each pathogen detection (qualitative; semi-quantitative using cycle threshold (Ct) values).b)Pain related to each sampling technique using the EVENDOL (EValuation ENfant DOuLeur; Evaluation Child Pain), a recognized and validated standardized pain assessment scale for children under 7 years of age [11]. It will be assessed by the caregiver.c)Caregiver and parental satisfaction related to each sampling technique using a 0–10 visual scale.d)Time spent by caregivers for each procedure (without considering the time needed for preparation and explanation).e)Complications associated with the sampling techniques: bleeding, irritation, and exposure of healthcare workers to biological agents.f)Procedural discrepancies associated with the two sampling techniques: involvement of multiple healthcare workers, repetition of the procedure, and cessation of care by the legal representative.g)Non-conclusive results according to the sampling technique: insufficient sample volume, refusal of sampling, and laboratory measurement errors.

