### Sample size

A review of the performance of saliva samples among adults and children by Laxton *et al*. reported concordance between saliva sampling and the reference comparator between 93 and 100%, depending on the studies and pathogens considered [12]. Accordingly, a 95% concordance is expected in our study. In the clinical context of bronchiolitis diagnosis, a 5% discordance (false-positive and false-negative results) is considered acceptable to validate the use of saliva samples instead of NPA. For a precision of 2% for the 95% confidence interval of the overall agreement (total interval length of 4%), it is necessary to analyze 457 patients. We estimate that a maximum of 10% of the children included will not be available for one of the two tests (insufficient sample volume, refusal of a second sample, etc.). It is therefore necessary to include 502 children.

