### Data analysis

The type I risk will be 5% for all analyses. The 95% confidence intervals (CI) will be estimated by non-parametric bootstrapping (1,000 resampling), especially because of the low prevalences of pathogens and the related non-gaussian distributions. No interim analyses are planned. No correction of the multiplicity of tests will be performed. The analysis of the secondary endpoints will therefore be considered exploratory.

Because we expect a low percentage of missing values and missingness is at random, complete case analyses will be performed, i.e., patients with a missing value on the NPA-based test or the saliva-based test will not be considered in the analyses. The baseline characteristics (listed in the previous subsection) of the excluded patients will be compared with those of the analyzed population. If we observe differences, i.e., a non-random process, the outcomes’ analyses will be based on multiple imputation to reduce the risk of bias due to missingness (50 imputed databases, and confidence intervals obtained from the 5,000 resulting bootstrap samples).

*Descriptive analysis.* A description of demographic and clinical characteristics will be provided using means and standard deviations for continuous characteristics, or percentages and effectives for categorical characteristics. This description will be performed for the overall sample and according to the overall agreement (primary outcome) of the saliva-based and the the NPA-based tests.

*Analysis of the primary outcome.* We will estimate proportion of overall agreement and the related 95% CI. The agreement will be the diagnostic the same pathogens in-between the NPA-based and the saliva-based tests. More precisely, consider the following table for a pathogen where . The overall agreement is defined as

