**Table utbl0002:** 

Effective (proportion)		Saliva-based test		Total
		Positive result	Negative result	
NPA-based test	Positive result	()	()	()
	Negative result	()	()	()
	Total	()	()	()

*Analysis of the secondary outcomes (a).* For each pathogen, the following estimations and related 95%CI will also be estimated with the use of NPA-based results as gold standards [13]. The positive and negative percent agreement are respectively equaled to and . The Cohen’s kappa coefficient is, where . Additionally, by considering the NPA-based as the reference, sensitivity and specificity are .and, respectively. In addition, positive and negative predictive values are and, respectively.

*Secondary outcomes (b-d).* The pain level, the parental satisfaction, and the time spent by caregivers will be compared according to the sampling technique (NPA versus Saliva) in terms of means by paired two-sample t-tests. The interaction with the order (saliva/NPA or NPA/saliva) will also be explored by mixed linear models.

*Secondary outcomes (e-g).* The causes of complications, procedural discrepancies, and non-conclusive results will be described in terms of frequencies and percentages. In addition, to compare the two techniques, the following three proportions will be estimated and compared by using McNemar test: i) the proportion of sampling with at least one event among the following complications: bleeding, irritation, and exposure of healthcare workers to biological agents; ii) the proportion of sampling which has necessitated multiple healthcare workers, repeated procedure, or cessation of care by the legal representative; iii) the proportion of interventions with non-conclusive results: insufficient sample volume, refusal of sampling, or laboratory measurement errors. The interaction with the order (saliva/NPA or NPA/saliva) will also be explored by mixed logistic models.

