### Limitations of the protocol

The primary outcome is the overall agreement between the two tests. The primary outcome will be affected by the microbial epidemiology of respiratory infections, which may vary each year. Even if some tendencies can be predicted in seasonality, the emergence of a new viral lineage or variant may occur [1,15]. The proportion of atypical bacteria, such as *Mycoplasma pneumoniae* and *Chlamydophila pneumoniae*, is also unpredictable, as they are known to cause epidemics every 5 to 7 years (16). This issue could be partially addressed by the 3-year study design, which will limit the impact of epidemiologic variations.

The required sample size was calculated according to this primary outcome, whose agreement can be inflated by many double-negative samples. The other results, i.e., discordant and double-positive samples, will be important to consider to better appraise the usefulness of saliva-based tests. Nevertheless, the related confidence intervals could be large.

The single-center study design may also affect the findings, as the standard of care and procedures may vary from those of other hospitals. This study should be considered a pilot study and, if the primary endpoint is achieved, will be followed by a randomized, multicenter national study for definitive validation of the use of saliva sampling in children with bronchiolitis or respiratory symptoms in pediatric departments.

Some patients may be excluded from the study if one of the two samples cannot be obtained or analyzed (e.g., if the volume is too low for analysis). A 10% loss of samples has already been considered when determining the sample size to address this issue. Moreover, the saliva sponge swab that will be used in this protocol has already been widely used in several studies and has proven successful in recovering enough saliva for further analyses.

Our study aims to evaluate the opportunity to replace NPA, the current reference approach in clinical practice, by saliva sampling. Importantly, NPA does not represent an absolute gold standard.

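### As worded, the complete-case rule drops children with a final failed sample from every analysis, including the comparison of non-conclusive results (secondary outcome g)

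*Protocol article*

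**What the plan says.** The Data analysis section of the protocol article opens with rules for the analyses as a whole (type I risk, bootstrap intervals, multiplicity). The missing-data rule stands among them, ahead of any individual outcome: "patients with a missing value on the NPA-based test or the saliva-based test will not be considered in the analyses". If the excluded children differ from the analysed ones at baseline, multiple imputation replaces the complete-case approach for the outcomes.

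Secondary outcome measures defines outcome (g) as "Non-conclusive results according to the sampling technique: insufficient sample volume, refusal of sampling, and laboratory measurement errors". For outcomes (e-g), Data analysis says that "the following three proportions will be estimated and compared by using McNemar test". The third of these is "the proportion of interventions with non-conclusive results: insufficient sample volume, refusal of sampling, or laboratory measurement errors".

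Sample size assumes that "a maximum of 10% of the children included will not be available for one of the two tests", with low volume and refusal of a second sample as its examples. Limitations of the protocol adds: "Some patients may be excluded from the study if one of the two samples cannot be obtained or analyzed". Data acquisition lists, among the items collected, whether a sample could not be retrieved.

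**The concern.** The rule and outcome (g) concern the same events. A child whose saliva volume was too small, whose second sample was refused, or whose sample never gave a valid result has a missing test and is also a case for (g). A rule that takes such children out of the analyses takes out what (g) is meant to count.

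This matters because agreement, estimated in children with two valid results, cannot show how often a technique gives no result. Outcome (g) is the planned formal comparison of that. The article presents feasibility of saliva sampling under two years of age as part of the study's value, and describes good sampling as hard to achieve at this age. For the same children, the rule also discards whatever was recorded on pain, satisfaction, time, complications and procedural discrepancies. One event in (f), the legal representative stopping the procedure, can itself be the cause of the missing result.

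**Working it through.** **1. The plan's own figures.** Inputs from Sample size: expected agreement p = 0.95, half-width h = 0.02, 95% interval.

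n = z² · p(1 − p) / h² = 1.96² × 0.95 × 0.05 / 0.02² = 456.17, rounded up to 457. This matches.

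456.17 × 1.10 = 501.8, rounded up to 502. This matches. The sample size is not in dispute.

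**2. Children expected to lack a result.** The allowance can be read two ways: 502 − 457 = 45, or 0.10 × 502 = 50.2, about 50. Both are upper figures, because the plan calls 10% a maximum.

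**3. Outcome (g) under the default rule.** McNemar's test uses only discordant pairs. For final results there are three cases:

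| NPA | Saliva | Role in (g) | Under the rule |
|---|---|---|---|
| conclusive | conclusive | no event | kept |
| one conclusive, the other not | | discordant pair | excluded |
| non-conclusive | non-conclusive | event on both | excluded |

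Both discordant cells are 0 for final failures, whatever the true failure rates. Failures rescued by a repeated procedure, or by the retest described under Primary outcome measure, leave no missing value. They could still be counted if first-attempt failures are scored, which the text does not settle.

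**4. Outcome (g) in all 502 children.** Assume each child without a result fails on one technique only. There are then up to 45 to 50 discordant pairs. The documents do not say how they would divide, so the splits below are assumptions (exact binomial test on discordant pairs):

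| Discordant pairs | Split between techniques | p |
|---|---|---|
| 50 | 25 / 25 | 1.00 |
| 50 | 30 / 20 | 0.20 |
| 50 | 35 / 15 | 0.007 |
| 50 | 40 / 10 | 0.00002 |
| 45 | 27 / 18 | 0.23 |
| 45 | 31 / 14 | 0.016 |

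The full analysis could show anything from no difference to a clear one. The analysis as worded gives no contribution from final failures in any of these rows.

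**5. Outcomes (b)-(d).** For one technique, mean in all children − mean in complete cases = f × d. Here f is the excluded share and d is the difference in mean between excluded and retained children. The documents give no value for d, so a range is assumed:

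| f | d = 1 point | d = 2 points | d = 4 points |
|---|---|---|---|
| 5% | 0.05 | 0.1 | 0.2 |
| 10% | 0.1 | 0.2 | 0.4 |

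The sign of d is not known.

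**The case against.** The strongest reply is that the rule was meant only for agreement. It speaks of a missing value on one of the two tests, which is a PCR result, whereas a failed sample is an observed value for (g). The paragraph on outcomes (e-g) makes sense only if failed interventions are in the denominator, and the retrieval failures are collected. This may well be the intent, but it is not written. The rule is placed before all outcomes, no outcome is exempted, and the limitations speak of exclusion from the study. This is a stated rule in conflict with a stated outcome, not a detail left to a later document.

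A second reply is that the imputation branch brings the children back. It may: the characteristics to be compared are those of the preceding subsection, and that list includes retrieval failure, which would differ between the groups almost by definition. But the branch is conditional, its trigger is loosely defined, and it is built for missing values. Outcome (g) is observed and needs no imputation.

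Other parts of the reply stand and limit the point. A reader might infer that (g) must come out as 0% against 0%. The documents do not support this, since rescued failures could remain and imputation could be triggered. A reader might also infer that (b)-(f) retain only successful procedures and so understate pain and complications. Repeated, difficult or complicated procedures stay in if both samples finally give a result. A refused second sample may have no second measurement for the paired t-test in any case. A laboratory failure says nothing about pain. Finally, nothing supports assigning all the failures to saliva.

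**Conclusion.** The conflict is real on the wording as it stands. Under the default analysis, all unresolved non-conclusive results leave the comparison of non-conclusive results, and no discordant pairs from final failures are left for its McNemar test. At most about 45 to 50 of 502 children are involved, if the plan's maximum loss is reached and each such child fails on one technique only. For (b)-(f), recorded data are lost for the same children. The direction of the effect is unknown, and for means its size is probably modest: 0.05 to 0.4 points over the assumed range.

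The primary estimate and the sample size are not affected. The plan declares its secondary outcomes exploratory, so this is a correction to the definition of analysis sets and does not threaten the trial's main result.

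**What to change.** State the analysis set for each group of outcomes:

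- Primary outcome and secondary (a): the complete-case rule and its imputation fallback apply here only.
- Secondary (g): all randomised children, with a final non-conclusive sample counted as an event for that technique. State also whether a failure later rescued by a repeat or retest counts.
- Secondary (b)-(f): all children for whom the relevant procedure data were recorded, whatever the PCR result.

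The planned tests can stay as they are. The cost is a sentence or two. The data are already on the collection list and no more children are needed. The change should be made before enrolment, so that the analysis set is not chosen after the failures are known.

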**Table utbl0002:** 

Effective (proportion)		Saliva-based test		Total
		Positive result	Negative result	
NPA-based test	Positive result	()	()	()
	Negative result	()	()	()
	Total	()	()	()

*Analysis of the secondary outcomes (a).* For each pathogen, the following estimations and related 95%CI will also be estimated with the use of NPA-based results as gold standards [13]. The positive and negative percent agreement are respectively equaled to and . The Cohen’s kappa coefficient is, where . Additionally, by considering the NPA-based as the reference, sensitivity and specificity are .and, respectively. In addition, positive and negative predictive values are and, respectively.

*Secondary outcomes (b-d).* The pain level, the parental satisfaction, and the time spent by caregivers will be compared according to the sampling technique (NPA versus Saliva) in terms of means by paired two-sample t-tests. The interaction with the order (saliva/NPA or NPA/saliva) will also be explored by mixed linear models.

*Secondary outcomes (e-g).* The causes of complications, procedural discrepancies, and non-conclusive results will be described in terms of frequencies and percentages. In addition, to compare the two techniques, the following three proportions will be estimated and compared by using McNemar test: i) the proportion of sampling with at least one event among the following complications: bleeding, irritation, and exposure of healthcare workers to biological agents; ii) the proportion of sampling which has necessitated multiple healthcare workers, repeated procedure, or cessation of care by the legal representative; iii) the proportion of interventions with non-conclusive results: insufficient sample volume, refusal of sampling, or laboratory measurement errors. The interaction with the order (saliva/NPA or NPA/saliva) will also be explored by mixed logistic models.

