## Description of protocol

### Study design

The PreSap study is a publicly funded, national, prospective, monocentric, randomized clinical trial comparing saliva samples and NPA in children between 28 days and 2 years old (Fig. 1). Once the protocol has been explained to the parents and child, and their agreement has been received, all patients will undergo the two sampling procedures after a randomization determining the order (crossover design with a 1:1 ratio). Randomization will be carried out with the REDCap software. Depending on the randomization, the saliva sample will be taken first or second, and the same will be done for the NPA. A rest period will be allowed between each sample so that the child can be calm again for the second sample. All temporal and behavioral data will be recorded.

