Randomization will determine the order in which the two procedures (saliva sampling and NPA) are performed. The interaction effect of the order will be tested in statistical analyses, particularly for criteria relating to the time taken to perform the procedure and the level of pain or satisfaction (secondary outcomes). For reasons of feasibility and ethics, we cannot plan a washout period long enough to prevent this type of interaction. In the event of a significant interaction, the results may be presented conditional on the first sampling.

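### The main test for pain, parental satisfaction and caregiver time has no term for the randomised order, so a first-to-second-sample shift inflates its error variance and, with unequal completers, biases the technique difference

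*Protocol article*

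**What the plan says.** Under Study design, the article states that "all patients will undergo the two sampling procedures after a randomization determining the order (crossover design with a 1:1 ratio". Under Data analysis, secondary outcomes (b-d), pain level, parental satisfaction and time spent by caregivers "will be compared according to the sampling technique (NPA versus Saliva) in terms of means by paired two-sample t-tests". The next sentence adds: "The interaction with the order (saliva/NPA or NPA/saliva) will also be explored by mixed linear models".

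The Limitations section returns to order. It will be tested "particularly for criteria relating to the time taken to perform the procedure and the level of pain or satisfaction (secondary outcomes"; the authors acknowledge that "we cannot plan a washout period long enough to prevent this type of interaction"; and "In the event of a significant interaction, the results may be presented conditional on the first sampling".

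On missing data, Data analysis specifies complete cases: "patients with a missing value on the NPA-based test or the saliva-based test will not be considered in the analyses". Sample size names refusal of a second sample as one reason for the loss of up to 10%. Secondary endpoints are declared exploratory.

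**The concern.** The protocol identifies time, pain and satisfaction as the outcomes that order may affect, and accepts that the interval between samples cannot rule this out. Yet the test it names for these outcomes pools all the NPA-minus-saliva differences as if they came from one population. Two consequences follow if the second sample scores systematically differently from the first.

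- **Precision.** The systematic gap between the two orders is treated as noise. Intervals are too wide and the test is conservative.
- **Bias.** If one order loses more children than the other, the shift no longer cancels and part of it is credited to a technique. This is plausible, since refusing the second sample may depend on whether the invasive procedure came first. The planned check on missingness compares the characteristics listed under Data acquisition. Randomised order is not on that list, so order-dependent loss need not trigger the multiple imputation.

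Better comfort for child and family is one of the main benefits the article claims for saliva sampling, so these comparisons will be read closely even though they are exploratory.

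**Working it through.** **Inputs from the article.** Two orders, 1:1 (Study design). Paired t-test without an order term (Data analysis). Type I risk 5%, taken here as two-sided. 457 children to analyse, 502 to include, at most 10% lost (Sample size). The 457 reproduces: 1.96² × 0.95 × 0.05 / 0.02² = 456.2, rounded up to 457. That figure concerns agreement only; no SD, target difference or power is given for outcomes (b)-(d).

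**Assumptions.** P is set at 0.25, 0.5, 0.75 and 1.0 times the within-order SD of the difference (σ = 1). The true technique difference τ is set to give about 80% power for the order-adjusted test, which is about 0.13 SD.

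**Model.** Let d be NPA minus saliva within a child. With a mean shift P from first to second sample, d centres on τ − P when NPA comes first (n_NF completers) and on τ + P when saliva comes first (n_SF completers). N is the total.

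**Paired t-test.**
- Expected estimate: τ + P × (n_SF − n_NF)/N.
- Variance it uses: σ² + P² × (1 − imb²), with imb = (n_SF − n_NF)/N. With balanced orders this is σ² + P².
- The true sampling variance of the mean, given the order counts, is only σ²/N.

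**Order-adjusted estimate.** The unweighted mean of the two order-specific mean differences. P cancels, and the standard error is (σ/2) × √(1/n_NF + 1/n_SF).

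**Balanced completers (228/229).** The ratio of interval widths is √(1 + P²). Worked case, P = 0.5: √1.25 = 1.118; power ≈ Φ(2.80 − 1.96 × 1.118) = Φ(0.61) ≈ 73%; false-positive rate ≈ 2Φ(−2.19) ≈ 2.8%. Simulation (20,000 trials per row) gives:

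| P/SD | CI too wide by | Paired t power | Paired t false-positive rate |
|---|---|---|---|
| 0.25 | 3% | 79% | 4.3% |
| 0.5 | 12% | 73% | 3.0% |
| 0.75 | 25% | 65% | 1.3% |
| 1.0 | 41% | 53% | 0.6% |

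The order-adjusted test stays near 80% power and 5% error in every row. A separate simulation with 226/226 completers gave about 78%, 73% and 52% power at P = 0.25, 0.5 and 1.0.

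**Unequal completers, moderate case.** Suppose 15% are lost in one order and 5% in the other, from 251 each: 213 and 238. Imbalance = 25/451 = 0.055, so the estimate moves by 0.055 × P. At P = 0.5 that is 0.028 SD. The adjusted standard error is 0.5 × √(1/213 + 1/238) = 0.047, so the shift is about 0.6 of a standard error. The paired t-test false-positive rate was simulated at 5.5%, 6.0%, 5.9% and 5.8% over the four values of P: the inflated standard error largely masks the bias in the test, but the estimate is still displaced.

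**Unequal completers, worst case.** If the whole 10% loss falls in one order (251/201), imbalance = 50/452 = 0.111. For P = 0.25, 0.5 and 1.0 the bias is 0.028, 0.055 and 0.111 SD, and the false-positive rate is about 8%, 16% and 34%. The order-adjusted test stays at about 5%.

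**Does the text already repair this?** In a two-order, two-sample design, the technique-by-order interaction is the period shift P. The planned mixed model therefore estimates P, but the article uses it only to explore the interaction and not as the source of the technique effect. The fallback in Limitations is optional and depends on significance. Read as within-order differences, its results estimate τ − P and τ + P, and neither isolates τ.

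**The case against.** The strongest reply is that order is not absent from the plan. A mixed model with order follows immediately after the t-test, and an adjusted technique effect could be read from it; the exact model terms might sit in an analysis plan that is not shown. That is fair as far as it goes, but the article fixes the t-test as the technique comparison and gives the model an exploratory role.

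Four further points limit the weight of the concern:

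- The power loss depends on a small true effect. At a true difference of 0.2 SD, paired t-test power is 98.9%, 98.2%, 96.9% and 93.6% over the four values of P, and at 0.3 SD it is about 100%. The trial claims no power for these outcomes.
- With balanced completers the test is unbiased and conservative, so it does not create a false claim for saliva. In the 213/238 case its error rate stays close to nominal.
- P is unknown. The planned rest period is meant to reduce it, and the article treats an order effect as a possibility and gives no size.
- The remedy assumes one common shift. If carryover differs by technique, the order-adjusted estimate is biased too, and it does not deal with selective refusal as such.

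All four stand as limits on size. None makes the unadjusted test the better choice. On the last, the paired t-test is exposed to the same carryover problem and handles the common shift less well.

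**Conclusion.** The concern holds. The named test omits the factor that the trial randomises and that the protocol flags for these very outcomes. With balanced completers the cost is precision: intervals 3% to 41% too wide for P between 0.25 and 1.0 SD, with the power loss passing 5 points from roughly P = 0.4 to 0.5 SD if the true effect is near 0.13 SD. With unequal completers there is also bias equal to P times the imbalance: 0.055 × P at 213/238, and 0.111 × P if all of a 10% loss falls in one order. The values of P, the true effect and the completer splits are assumptions, because the documents give none. The endpoints are exploratory and the primary agreement outcome is untouched, so this is an inexpensive improvement that should be made; it does not threaten the trial's main conclusion.

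**What to change.** In Data analysis, secondary outcomes (b-d), replace the paired t-test with the order-adjusted crossover comparison: the unweighted mean of the two order-specific mean differences (NPA minus saliva), with the pooled within-order variance. With complete pairs, the same estimate comes from a mixed model with technique, period (first or second sample) and a random intercept for child, which is a small extension of the model already planned. State that this is the technique comparison whatever the interaction test shows. For these outcomes, stratify the bootstrap by randomised order. Reporting completers by order would let readers judge the imbalance.

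The cost is a change of wording and one degree of freedom. Order is already randomised, so no extra children or measurements are needed.
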